### Cameroon

Soa and Mbankomo are peri-urban areas located on the north-eastern and south-western periphery of Yaoundé, respectively (Fig. 2). Both areas have an estimated population density of 1,235 people per squared km and 15% of the population is under 5 years of age. In total, there are 39 health facilities in Soa, 12 of which are public and 28 have active CHWs. Of the 39 facilities, 20 administer EPI services and are eligible for SP administration as part of the expanded PMC programme. In Mbankomo, there are 32 health facilities, of which 4 are public and 10 have active CHWs. Of the 32 facilities, 19 administer EPI services and are eligible for SP administration as part of the standard of care PMC programme. Malaria incidence in both Soa and Mbankomo was 597 cases per 1000 children under 5 in 2020 [12]. Malaria transmission is typically highest during the two rainy seasons, from March to June and from October to November.

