### Côte d’Ivoire

Séguéla and Kani are rural areas located approximately 500 km northwest of the capital city, Abidjan (Fig. 2). The estimated population density is 45.98 people per squared km (2021) and 18% of the population is under 5 years of age. In total, there are 42 health facilities in Séguéla, all of which are public and 33 of these have active CHWs. Of the 42 facilities, 41 administer EPI services and thus are eligible for SP administration as part of the expanded PMC programme. In Kani, there are 8 health facilities, all of which are public and have active CHWs. Of the 8 facilities, all administer EPI services and thus would be eligible for SP administration if any doses were given as part of a standard of care PMC programme. According to the NMP, malaria incidence in both Séguéla and Kani was 572 cases per 1000 children under 5 in 2020 with the peak typically from April to July during the rainy season.

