### Sample size

For the passive cohort, we will monitor all eligible children enrolled in the study and will therefore, will constitute a population sample. For the active cohort, the sample size was calculated to ensure 80% power at the 5% significance level, assuming an intra-cluster correlation coefficient of 0.25, and accounting for a 3:1 sampling ratio of intervention to control to ensure sufficient power to assess any variation in PMC effectiveness according to distance to the EPI facility. However, the specific sample size for the number of EPI facilities and children to include in the active cohort was calculated separately for each study site to account for the differences in PMC implementation (Fig. 1).

In Cameroon, we expect a 30% reduction in malaria incidence in intervention compared to control areas, requiring 26 intervention and 9 control EPI facilities are required. With a 20% expected loss to follow-up rate, we require 1,560 in the intervention and 540 children in the control area over the 18 months of observation in the active cohort. In Côte d’Ivoire, the standard of care currently being implemented by the NMP is no doses, so the difference between in the number of SP contacts between arms is 5. Therefore, we expect a 40% reduction in malaria incidence in intervention compared to control areas. Accordingly, 14 and 5 EPI facilities will be required in the intervention and control areas, respectively. Assuming a conservative loss to follow-up rate of 20%, we require 1,148 and 410 children in the intervention and control areas, respectively, over the 18 months of observation in the active cohort.

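### Cameroon's 26 intervention EPI facilities cannot be drawn from Soa's 20; moving the six missing facilities to Mbankomo would more than recover the lost power with the same children

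*Protocol article*

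**What the plan says.** The sample size section of the protocol article aims for 80% power with a 5% test. Clustering enters through one figure, "assuming an intra-cluster correlation coefficient of 0.25". Three intervention children are sampled for each control child, and the reason given for this ratio is "to ensure sufficient power to assess any variation in PMC effectiveness according to distance to the EPI facility".

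For Cameroon (expected reduction 30%) it requires 26 intervention and 9 control EPI facilities, with 1,560 and 540 children, which is 60 per facility in both arms. For Côte d'Ivoire (expected reduction 40%): "Accordingly, 14 and 5 EPI facilities will be required in the intervention and control areas, respectively". The child numbers there are 1,148 and 410, which is 82 per facility in both arms. Both child totals allow for 20% loss over 18 months.

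The site descriptions give the facilities on hand. Soa (intervention, Cameroon) has 20 with EPI services. For Mbankomo (control), "Of the 32 facilities, 19 administer EPI services". Séguéla (intervention, Côte d'Ivoire) has 41, and for Kani (control), "Of the 8 facilities, all administer EPI services". The study design section makes every EPI facility in the sites eligible, selects among them at random and names them the primary sampling unit.

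**The concern.** The Cameroon requirement exceeds what Soa has by six facilities, so the stated design cannot be run as written. Spreading the 1,560 children over 20 facilities (78 each) is the obvious repair, but it leaves 9 control facilities as the weak side of the comparison while 10 Mbankomo EPI facilities stay outside the sample.

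In a comparison of clusters, a small arm with few clusters sets the precision: further children in the same facilities reduce only the within-facility part of the variance. At stake is the precision of the primary rate comparison, and how far it rests on a handful of control catchments. The same structure, in milder form, is present in Côte d'Ivoire with 5 of Kani's 8 facilities.

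**Working it through.** **Inputs.** From the sample size section: rate ratios 0.70 (Cameroon) and 0.60 (Côte d'Ivoire), 18 months, 20% loss, and the facility and child numbers above. Assumed: control rates 0.597 and 0.572 per child-year (the 2020 under-5 figures in the site descriptions; the article does not say they were used), a two-sided test, and 0.25 read as the between-facility coefficient of variation k.

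**Formula, rate difference.** V = [λ0/y0 + (kλ0)²]/c0 + [λ1/y1 + (kλ1)²]/c1, where c is facilities per arm and y = children per facility × 0.8 × 1.5. Then z = (λ0 − λ1)/√V and power = Φ(z − 1.96). The t version uses a non-central t on c0 + c1 − 2 degrees of freedom.

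**Reproducing the stated sizes.** At 3:1 and 80% power the formula asks for 26.5/8.8 facilities in Cameroon (stated 26/9) and 13.4/4.5 in Côte d'Ivoire (stated 14/5). Power at the stated numbers is 80.5% (t 78.1%) and 83.8% (t 79.3%). Read literally as an intra-cluster correlation, with the 2020 figures as risks, 0.25 gives only 44.8% and 41.9%. The coefficient-of-variation reading is therefore used below.

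**Cameroon, Soa limited to 20 (λ0 = 0.597, λ1 = 0.4179, difference 0.1791).**
- 20/9: y0 = 60 × 1.2 = 72; y1 = 78 × 1.2 = 93.6. Control: (0.008292 + 0.022276)/9 = 0.003396. Intervention: (0.004465 + 0.010915)/20 = 0.000769. V = 0.004165, z = 2.78, power 79.2% (t 76.3%). The control arm is 82% of V, and its between-facility part is 2.7 times the Poisson part.
- 20/15, same children: y0 = 36 × 1.2 = 43.2. Control: (0.013819 + 0.022276)/15 = 0.002406. V = 0.003175, z = 3.18, power about 89% (t 87%).

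Losing six intervention facilities costs about 1 point (80.5% to 79.2%). Placing six in the control arm gains about 10.

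**Côte d'Ivoire (λ0 = 0.572, λ1 = 0.3432, difference 0.2288).**
- 14/5: V = 0.005252 + 0.000775 = 0.006027, z = 2.95, power 83.8% (t 79.3%). The control arm is 87% of V.
- 11/8, same children (about 104 and 51 per facility): V = 0.003719 + 0.000918 = 0.004637, z = 3.36, power 91.9% (t 88.6%).

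**Log rate ratio.** This is the scale of the Poisson model in the data analysis section. V = [1/(λ0y0) + k²]/c0 + [1/(λ1y1) + k²]/c1 and z = −ln(rate ratio)/√V.
- Cameroon: 20/9, SE 0.1180, z = 3.02, 85.6%; 20/15, SE 0.1056, z = 3.38, 92.2%. The SE falls by 11%.
- Côte d'Ivoire: 14/5, SE 0.1504, z = 3.40, 92.4%; 11/8, SE 0.1384, z = 3.69, 95.8%. The SE falls by 8%.

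**Dependence on k (rate difference, z).**

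| k | Cameroon 20/9 → 20/15 | Côte d'Ivoire 14/5 → 11/8 |
|---|---|---|
| 0.15 | 96.6 → 98.5% | 98.5 → 99.5% |
| 0.20 | 89.8 → 95.2% | 93.4 → 97.3% |
| 0.25 | 79.2 → 88.8% | 83.8 → 91.9% |
| 0.40 | 48 → 61% | 51 → 64% |

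**The case against.** The strongest reply is that, apart from the facility count in Soa, no error is shown. The plan sets 80% power, and on the reading used here its stated numbers give 80.5% and 84%; more than that is an efficiency preference. This stands for Côte d'Ivoire, which is why the change there is optional. In Cameroon the stated numbers cannot be realised, so some change is needed anyway.

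A reader might infer that the Cameroon study is underpowered, or that a gain of 8 to 10 points is established for both countries. The documents support neither. The shortfall at 20/9 is about one point (four with the t reference) and appears only on the rate difference; on the log rate ratio 20/9 stays above 80%. The size of the gain rests on an assumed control rate and on a reading of 0.25 that differs from the article's own label, and it shrinks on the log scale and with smaller k. Nor are control children concentrated more heavily than intervention children: the take per facility is equal in both arms.

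Four further points stand.
- More control facilities do not replicate the district. With an illustrative between-district coefficient of variation of 0.10 (an assumption), V rises by 0.01 × (λ0² + λ1²). Power then moves only from 45.2% to 49.4% in Cameroon and from 60.8% to 67.0% in Côte d'Ivoire.
- Against the 29 catchments achievable in Cameroon, 20/15 is a real addition of six.
- Selection may be finished: the Fig. 2 legend speaks of selected facilities, although the study design section uses the future tense. Fig. 3, which gives facility numbers and design-stage exclusions, is not shown, so some of the Mbankomo or Kani facilities may be unavailable.
- The distance objective is the stated reason for 3:1. The proposal leaves the ratio of children as planned, but in Côte d'Ivoire it drops three intervention catchments, and the effect on that objective has not been assessed.

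**Conclusion.** The point holds as a limited improvement in design, with one inconsistency at its root: 26 facilities are required where 20 exist. If the six are drawn in Mbankomo, Cameroon gains about 10 points on the rate difference (79% to 89%; t 76% to 87%) or about 7 on the log rate ratio (85.6% to 92.2%), with the same children and the planned total of 35 facilities. In Côte d'Ivoire the gain is about 8 points on the rate difference but only about 3 on the log rate ratio.

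These figures assume k = 0.25, the 2020 rates as control rates, equal children per facility within each arm, and no variation between districts. On the rate difference the gain is about 1 to 5 points for k of 0.15 to 0.20 and about 13 at k = 0.4. The direction is firm under the article's facility-level model; the size is not.

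**What to change.** **Cameroon.** If facility selection can still be amended, replace 26/9 by 20/15: all 20 Soa EPI facilities (78 children each for the 1,560) and a random 15 of Mbankomo's 19 (36 each for the 540). Restate the power, saying whether 0.25 is a correlation or a coefficient of variation, which control rate was used, and on which scale the test is planned. The cost is an amendment plus household census, three-monthly updates and passive monitoring in six more control catchments than the 29 achievable, though none beyond the planned 35. No extra children are needed. The added catchments should be in place before the initial census, which the article puts ahead of PMC implementation.

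**Côte d'Ivoire (optional).** Draw all 8 Kani facilities with about 51 children each and 11 in Séguéla, keeping 19 facilities and 1,148/410 children. The cost is three fewer intervention catchments and about 104 children, instead of 82, in each of the 11. The article gives no catchment sizes, so this take must be checked for feasibility first.

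**If selection is closed.** Correct the 26 and restate the power for the facilities actually available.

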### Consenting procedures

During the census written informed consent will be obtained from the head of household and the primary caregiver of each eligible household and child. The potential participant will be reassured that refusal to participate or withdraw from the study at any point will have no impact on access to EPI vaccinations, PMC or routine health care. The head of household and/or primary caregiver will then be asked to sign the form as consent for their household and any eligible children to participate in the study, respectively. If the potential signatory is unable to sign, an independent adult witness not involved in the study, will sign on their behalf and the head of household or primary caregiver will provide a thumbprint marking their consent. If the signatory of a household/child is below the age of majority, defined as a person who is at least 21 in Cameroon and 18 years of age in Côte d’Ivoire, they will be asked to provide assent to confirm their willingness for their household/child to participate in the study in addition to consent from an appropriate person of legal age. A second consent form will be completed for permission for long-term storage and future use of the samples collected. Any amendments to the study protocol will be approved by all relevant ethics review boards and participants will provide additional consent, as described above, for the changes.

### Data analysis

The primary analysis will be based on intention to treat (ITT), including all children residing in the intervention area as the exposed group. All available data up to the time of censuring (e.g., loss to follow-up, withdrawal, death, or study completion), irrespective of whether the child received any, part, or all the intended PMC doses. An additional per-protocol analysis will be completed which includes children who received at least one dose, all doses, or specific doses of PMC. The period of protection provided by SP is up to one-month post treatment and thus will constitute the protective window of those receiving the intervention. Data for both countries will be combined for analysis as well as assessed separately to ensure context specific nuances are fully assessed.

Incidence rates for malaria and anaemia will be calculated using multivariable Poisson regression, difference-in-difference, and interrupted time-series models comparing intervention and control areas [14–16]. Incidence rates, rate differences, and rate ratios between intervention and control area will be calculated for the ITT and per-protocol analysis. Malaria incidence will be determined by the number of malaria cases confirmed by either RDT or microscopy identified in either the passive or active cohort. Person-time at risk for each study outcome will be calculated based on the date of recruitment into the study population until the date of censuring or study end. For children who leave the study prior to the end date, the date of exit will be the date where they moved, withdrew from the study, or died. If that date is not known, the midpoint between the date of last contact and the date the loss was detected will be used. Protective effectiveness will be calculated for the intervention period including the 18 months of follow-up for the periods where PMC doses differ, stratified by first and second year of life, as well as during the post-intervention period, starting at 24 or 18 months of age in Cameroon and Côte d’Ivoire, respectively, to estimate any potential rebound in malaria.

Where there are repeated measures per child, random effects or generalising estimating equations models will be used to adjust for non-independence of the data from the same individual. Regression models will assess factors associated with incidence of malaria infection including demographic variables, malaria history, reported vector control use, socio economic position, amongst others [17]. Transmission intensity, type of PMC delivery mode, impact of the estimated protective window of SP, and other factors will be adjusted for to assess their impact on the incidence trends [18]. Subgroup analysis will constitute assessing the impact of distance to the health facility as a proxy for access to health services according to the study endpoints highlighted above. Distance will be assessed according to tertials of distance of all study participants to their nearest health facility and as a continuous variable. Alternate model forms including interaction terms as well as semiparametric approaches to account for time-varying intervention effects to account for the expected 4-week prophylactic period of SP will be tested [19]. Because of the challenges in confirming cause of death in those who die in the community and the assumption that severe malaria cases will seek care at a health facility, only the passive cohort data will be used to assess these secondary outcomes [20]. An interim analysis will be conducted after the 4th active cohort visit and the study will be reported according to the ‘Strengthening the reporting of observational studies in epidemiology’ (STROBE) guidelines [21].

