### Aims and objectives

This is a multi-site study with the primary aim to evaluate the impact of routine delivery of PMC on malaria incidence during the first two years of life. In Cameroon we will compare the effect of up to eight versus the standard of care of five doses, whilst in Côte d’Ivoire we will compare the effect of five versus zero SP doses, as the standard of care. Secondary objectives include determining any differences in: (i) severe malaria, malarial deaths, anaemia, and severe anaemia; (ii) differences in all indicators by country, delivery platform and the number and timing of doses; and (iii) any dose response effect or differences according to distance to the health facilities, as a proxy for access to care.

Evaluation of malaria interventions requires knowledge of the regional epidemiology of malaria and active and passive surveillance methods have been proposed for malaria vaccine efficacy studies. Passive case detection methods are limited to those seeking health care and are likely to underestimate burden of malaria in the community but may provide information on the clinical presentation and management of malaria relevant for planning health services. In contrast, active surveillance methods can minimise the effect of health care-seeking behaviour on malaria detection and measures of effect. It also allows for understanding the age, spatial and temporal patterns of disease in community settings. To address these issues, we will employ two approaches to address the study objectives. First, we will develop a passive cohort, which will capture routinely collected health data as part of all child visits to participating health facilities in the selected study sites. Secondly, we will form and prospectively follow an active cohort of children who will be visited at their households every three months over the study period. Reported malaria and anaemia cases in children under 5 years from the 5 years prior to the start of the study will also be collected to ensure results can be interpreted within the context of the broader malaria transmission patterns at each site.

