## Methods

### Study site

Areas with the highest malaria transmission in both Cameroon and Côte d’Ivoire were purposively selected to be PMC implementation areas to maximize any observable impact of the intervention. Control areas in both countries were also identified that had epidemiological profiles that were similar to the intervention areas. In Cameroon, we chose Soa and Mbankomo in the Central Region as the intervention and the control areas, respectively, whilst in Côte d’Ivoire, Séguéla and Kani in the Worodougou Region were chosen as the intervention and control areas, respectively. These sites were chosen based on the size of the population, number of EPI facilities, malaria incidence, EPI coverage, and availability of a suitable control population receiving standard of care (Fig. 2).

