### Passive cohort

All children up to 36 months of age residing in enumerated households during the census will be eligible for inclusion in the passive cohort and enrolled upon provision of written informed consent from their primary caregiver (Table 1). Enrolled children will be passively monitored to record both EPI vaccinations and PMC visits as well as clinical visits for malaria and anaemia to the health facility and/or CHWs over the 18-month study period. Older children (24 to 36 months at baseline) are not eligible to receive the intervention but will be enrolled in this study activity for two reasons: first, the older children will serve as an internal control as it is assumed that they will experience a similar malaria transmission intensity but will not receive the intervention and, secondly, as children will be followed for 18 months information will be available on children who age-out of eligibility to assess any impact beyond when children are eligible to receive PMC. Children will not be censored according to age.

During the passive cohort recruitment, trained fieldworkers will record basic demographic information about the child, recent malaria cases, amongst other information. An anonymous and unique QR code with the participant ID linked will be attached to each child’s health and vaccination record books. This QR code will be used to identify children participating in the study when they interact with the health system and facilitate linking the data generated by the routine system on EPI, PMC or clinical visit, which are stored in separate registers, with the research activities. During recruitment, the national health ID number assigned to each child and written in the health and/or vaccination record books will be recorded. The names of children and primary caregivers will also be recorded to provide a means to verify that children present match ID numbers. This also serves as a back-up method to link health information data that is routinely collected in different registers. Caregivers will be encouraged to take children to the participating facilities or CHWs to receive EPI vaccinations or PMC or for any illnesses.

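### The primary ITT definition has no age limit, so read literally it counts the 24-36-month-old internal control as exposed, and the protocol does not say whether its age-limited estimate is the primary one

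*Protocol article*

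**What the plan says.** All references are to the protocol article.

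- **Aims and objectives.** The primary aim is the "impact of routine delivery of PMC on malaria incidence during the first two years of life".
- **Passive cohort.** Children up to 36 months are enrolled and followed for 18 months. "Older children (24 to 36 months at baseline) are not eligible to receive the intervention", but they are enrolled, first because "the older children will serve as an internal control" and second so that follow-up covers children who age out. "Children will not be censored according to age".
- **Data analysis, ITT.** The primary analysis is by intention to treat, "including all children residing in the intervention area as the exposed group". Malaria cases are those "identified in either the passive or active cohort". Person-time is "calculated based on the date of recruitment into the study population until the date of censuring or study end". Reaching a given age is not among the listed reasons for censoring.
- **Data analysis, effectiveness.** The same section later says that protective effectiveness covers the part of follow-up in which the dose schedules differ, split by first and second year of life. A post-intervention period is reported separately, from 24 months of age in Cameroon and 18 months in Côte d'Ivoire. This estimate is not labelled primary.

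**The concern.** The census precedes PMC implementation, so a child already aged 24 months at baseline cannot receive PMC during the study. Such a child in the intervention area is exposed under the ITT sentence and a control under the passive cohort section. Both cannot hold in one analysis.

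Followed as written, the ITT rate ratio would also take in person-time up to 54 months of age (36 + 18), well beyond the age range in the primary aim. Much of that time could not benefit, so the ratio would move towards 1. The post-intervention period has a related problem. It is defined by age alone, so children who never received the programme could be mixed with those who aged out of it, which would blur the estimate of rebound.

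The protocol does not say whether the primary rate ratio is the all-children comparison or the age-limited one. The two can give quite different answers to the same policy question, so the choice should be fixed before results are seen.

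**Working it through.** The protocol gives no figure for the age make-up of the ITT set, so there is nothing to reproduce. The check asks how far the two readings could differ.

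**Inputs from the protocol.** Passive-cohort age at census is up to 36 months. Follow-up is 18 months. The post-intervention period starts at 24 months (Cameroon) or 18 months (Côte d'Ivoire). Expected reductions are 30% and 40%, that is, rate ratios of 0.70 and 0.60 (Sample size). Active-cohort recruitment ages are 6-9 months and 10 weeks to 6 months.

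**Assumptions, not in the protocol.** Baseline ages are uniform over 0-36 months, with one child per month of age. There is no loss to follow-up. Incidence is equal at all ages. The full effect applies below the age cut and none above it. Two cases are shown: a closed cohort, and one that also adds births at one per month, since the census updates record births.

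**Step 1: share of passive-cohort person-time below the cut.** A child aged a at baseline contributes min(18, max(0, c − a)) months below age c.

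- Total, closed cohort: 36 × 18 = 648 child-months.
- Below 24 months: 6 × 18 + 18²/2 = 108 + 162 = 270, so 270/648 = 41.7%.
- Below 18 months: 18²/2 = 162, so 162/648 = 25.0%.
- Births add 18²/2 = 162 child-months, all below 18 months of age. The shares become (270 + 162)/(648 + 162) = 432/810 = 53.3% and (162 + 162)/810 = 40.0%.

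**Step 2: pooled rate ratio.** With s the share below the cut, observed RR = 1 − s × (1 − true RR).

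| Country (cut) | True RR | Closed cohort | With births |
|---|---|---|---|
| Cameroon (24 months) | 0.70 | 1 − 0.417 × 0.30 = 0.875 | 1 − 0.533 × 0.30 = 0.84 |
| Côte d'Ivoire (18 months) | 0.60 | 1 − 0.25 × 0.40 = 0.90 | 1 − 0.40 × 0.40 = 0.84 |

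If the effect in Côte d'Ivoire lasted to 24 months, the last row would read 1 − 0.417 × 0.40 = 0.83 and 1 − 0.533 × 0.40 = 0.79.

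**Step 3: the internal-control children alone.** Those aged 24-36 months at baseline supply 12 × 18 = 216 child-months, which is 216/648 = 33.3% (closed) or 216/810 = 26.7% (with births). If they were the only unexposable person-time in the exposed group:

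- Cameroon: 1 − 0.667 × 0.30 = 0.80, or 1 − 0.733 × 0.30 = 0.78.
- Côte d'Ivoire: 1 − 0.667 × 0.40 = 0.73, or 1 − 0.733 × 0.40 = 0.71.

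**Step 4: the active cohort.** It recruits no child aged 24-36 months. Ages are taken as uniform within the recruitment range.

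- Cameroon: mean recruitment age is 7.5 months, so mean time past 24 months is 7.5 + 18 − 24 = 1.5 of 18 months. That leaves 91.7% below 24 months, and 0.70 would read 1 − 0.917 × 0.30 = 0.725.
- Côte d'Ivoire: 10 weeks is 10/4.345 = 2.30 months, so mean recruitment age is 4.15 months and mean time past 18 months is 4.15 of 18. That leaves 76.9% below 18 months, and 0.60 would read 1 − 0.769 × 0.40 = 0.69. All of its person-time is below 24 months.

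**The case against.** The strongest reply is that the Data analysis section should be read as a whole. The ITT sentence is ordinary wording about doses received: it continues by keeping children in whatever number of doses they had. The absence of age censoring is a rule for follow-up, and its stated purpose is to observe children who age out. Protective effectiveness is then limited to the periods in which doses differ, later ages are reported apart, and the aim itself is limited to two years. On that reading nothing is diluted.

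Much of this stands. A reader might infer that the primary result will be diluted, or that the protocol sets two rival primary contrasts. The documents support neither: the effectiveness sentence may simply specify the periods for the ITT effect. What it does not do is say so. The label primary is attached to the all-children definition, rate ratios are promised for that ITT set, and nothing removes the older children from it.

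A reader might also infer that the older children are not used to separate PMC from district, given that the intervention areas "were purposively selected to be PMC implementation areas to maximize any observable impact of the intervention". That goes too far. Difference-in-difference models are listed, although the groups to be differenced are not named. The protocol describes the control areas as epidemiologically similar and gives the same 2020 incidence for both areas in each country (597 and 572 per 1000 children under 5).

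It can also be said that age windows are commonly left to an analysis plan. That would answer a missing detail. Here the protocol states an exposed group that conflicts with its own control group and aim.

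**Conclusion.** The point holds as an inconsistency in the definition of the primary analysis. Read literally, the primary ITT rate ratio counts the internal-control children as exposed and goes beyond the first two years of life. The protocol does not say whether that ratio or its age-limited estimate is primary.

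Dilution is conditional on pooling all ages. In that case the passive-cohort ratio would move from 0.70 to about 0.84-0.88 in Cameroon and from 0.60 to about 0.84-0.90 in Côte d'Ivoire. These figures depend on the assumed age structure, equal incidence by age and no effect after age-out, none of which the protocol gives. They should not be applied to the active cohort, on which power is based. Under the same assumptions its ratios would be about 0.73 and 0.69.

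**What to change.** 1. State that the primary ITT rate ratio is the age-limited one. It uses person-time in the periods when doses differ between areas, up to the plan's own start of the post-intervention period (24 months in Cameroon, 18 months in Côte d'Ivoire), regardless of doses received.
2. Exclude children aged 24-36 months at baseline from the exposed group and from the post-intervention rebound estimate.
3. Use those children only as the internal comparison, for example in the difference-in-difference already listed (area by eligible age), as a supporting analysis. It does not have to become the primary model.

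The cost is small: revised wording, splitting existing follow-up by age, and less person-time in the primary estimate. No new data are needed.
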